## Abstract

**Background:**

Making Every Contact Count’ (MECC) is a person-centred initiative that enables service providers across settings to support behaviour change through conversations about health and wellbeing. MECC has been widely implemented across the UK and internationally, although training approaches vary considerably and do not consistently translate into MECC delivery. Evidence suggests that Healthy Conversation Skills (HCS) training, which supports service users to identify their own solutions, may be an acceptable and effective means of delivering MECC across settings. This realist evaluation aims to understand which elements of HCS training work, for whom, under what circumstances, in what respects, to what extent, and why, to inform the adaptation of HCS across settings to ensure that all recipients are equipped to deliver MECC.

**Methods:**

This mixed-methods realist evaluation will comprise pre- and post-training surveys (at baseline, immediately post-training, and approximately eight weeks post-training) and realist interviews. Two participant groups were selected for comparison: service providers working or volunteering in the voluntary, community, and social enterprise (VCSE) sector, and undergraduate pharmacy students. Initial programme theories were developed through abductive reasoning, literature scoping, and stakeholder engagement. Survey data will assess outcomes of HCS training, while realist interviews will explore how these outcomes are generated by underlying mechanisms within specific contexts.

**Discussion:**

A refined programme theory will be produced, explaining how and why HCS training leads to MECC delivery across different settings. Findings will inform how HCS training can be adapted for distinct audiences, identify the core components of MECC training that must be preserved, and guide future evaluations by examining whether HCS training translates into sustained MECC delivery. The findings of this study will inform resource allocation for preventative health interventions outside of healthcare settings and thus have the potential to shape public health policy, empower non-specialist providers, and strengthen strategies for disease prevention.

## Introduction

The World Health Organisation has described interventions that target smoking, alcohol intake, physical activity, and diet as amongst the ‘best-buys’ in reducing the rising incidence of non-communicable diseases (NCDs) and their associated costs [1]. Whilst upstream interventions that address the structural drivers of the rise of NCDs are key to addressing them (e.g., political, economic, or policy changes such as smoke-free legislation) [2], progression of upstream interventions is slow and faces several barriers including conflicting political interests with evidence, and opposing public opinion [2]. Downstream interventions (including individual level interventions) can support people to make changes to their behaviour and create a culture change towards prevention rather than treatment of diseases [3,4]. Concurrently, in the United Kingdom (UK) the most recent 10-Year Health Plan continues to promote person-centred care (placing individuals’ needs and wants at the forefront) and autonomy (encouraging individuals to be actively involved in their health and wellbeing) [3].

Making Every Contact Count (MECC) is a person-centred intervention that aims to utilise existing conversations to promote health behaviour change [5] (see Table 1 for a summary of key terms). Its alignment with strategic focuses of prevention and autonomy mean that MECC continues to be implemented across the UK and beyond, since it became compulsory in 2016 that all NHS staff are trained to deliver MECC to their patients [5]. A unique feature of MECC is that it does not require its deliverers to be specialists in behaviour change or healthcare professionals. It’s approach, resembling motivational interviewing through asking open questions as opposed to providing advice, means that in theory anyone can deliver and receive MECC [6]. Within the wider framework of individual-level behaviour change interventions, MECC is conceptualised as a low-intensity, opportunistic behaviour change intervention [5]. NICE guidance on individual-level behaviour change (PH49) distinguishes between very brief, brief, extended brief, and high-intensity interventions, delivered according to an individual’s level of need [7,8]. MECC is typically categorised within the lower-intensity end of this continuum, spanning very brief and brief interventions [5]. As such, MECC conversations may range from a matter of seconds to 30 minutes and support self-management, requiring signposting or referral to more specialist services where more complex or sustained support is required [5,8]. Thus, MECC is positioned as an entry-point within a broader behaviour change system.

**Table 1 pone.0346348.t001:** A summary of key terms around the topic of this realist evaluation (opportunistic behaviour change conversations).

Term	Definition
Very brief intervention	A low intensity intervention lasting between seconds and minutes.
Brief intervention	A low intensity intervention lasting around 15–30 minutes.
Opportunistic behaviour change conversations	Utilising existing conversations to talk about health and wellbeing (or topics related to health and wellbeing, e.g., the social determinants of health) and encourage positive behaviour change through the use of behaviour change techniques (e.g., advice, support, signposting). Sits within brief and very brief interventions.
Making Every Contact Count (MECC)	A specific approach to opportunistic behaviour change conversations which is guided by topics or behaviours that are important to the individual.
Healthy Conversation Skills (HCS)	A specific approach to MECC training which focuses on key competencies (active listening, reflection, asking open discovery questions, and facilitating SMARTER goal setting) underpinned by a philosophy around motivating individuals to identify their own solutions. Typically delivered across three sessions lasting three hours each.
HCS ‘lite’	The specific iteration of HCS training under evaluation within this study. Adapted from original HCS training to a single session lasting three hours, whilst still covering the competencies and underlying philosophy.

Subsequently, MECC has been implemented across a range of settings outside of healthcare, including fire and rescue, local authorities, and the voluntary, community, and social enterprise (VCSE) sector [9,10]. However, it is noteworthy that there is a lack of evidence to support sustained behaviour change in recipients of MECC. To date, there has only been one fully powered controlled trial which was not randomised [11]. There remains a need for a fully powered trial that examines the effectiveness of MECC for the general population, to determine optimal allocation of health and social care funding to reduce NCDs. However, given the varied approaches to MECC training, understanding training mechanisms is foundational to ensure that MECC training facilitates delivery of MECC across settings, before investing in costly effectiveness trials.

A frequent challenge with implementing MECC is the barriers to service providers delivering MECC to patients following MECC training [12,13]. Frequently reported barriers to delivery of MECC across settings include lack of time [12,14–18], a perception that MECC is not part of the service providers’ role [12,15,16,19], and lack of confidence [9,12,15]. Compounding this challenge, MECC has until recently been poorly defined [6], and subsequently the content of MECC training varies widely across regions, with many regions developing their own training programme [15]. In accordance with national guidance for MECC training [20], many MECC training programmes focus on providing information to enable service providers to provide brief advice and signposting [4,21,22]. By contrast, Healthy Conversation Skills (HCS) is a specific approach to MECC training that reflects motivational interviewing skills [23]. Thus, it complements the recently agreed definition of MECC amongst experts [6]. It is also the most appropriate and empirically supported available training, having been repeatedly demonstrated to increase confidence [24,25] and competence [23,24,26–28] of service providers to deliver MECC, encouraging MECC delivery [27]. HCS is also the most feasible approach to deliver MECC at scale, as its avoidance of advice provision makes it appropriate for service providers who are not healthcare professionals and therefore do not feel confident enough or willing to provide advice.

However, the broad application of HCS across settings requires nuanced investigation, as it is conceivable that HCS training impacts different audiences in different ways. For example, service providers from the VCSE may require experiential learning, whereas healthcare professionals may be more comfortable with a ‘see one, do one’ approach [29]. Equally, service providers from the VCSE often feel confident in signposting but may feel unsure about proactively facilitating goal setting [30], whereas healthcare professionals may be familiar with goal setting but find it difficult to avoid providing advice [31]. Also, initially delivered across three separate sessions of three hours each, HCS has also been shortened to one three-hour session (HCS ‘lite’), although this shortened iteration has yet to be evaluated. Whilst this facilitates the delivery of HCS training at scale, as multiple sessions may be simply unfeasible for many VCSE organisations, it is uncertain whether it is sufficient to encourage recipients to deliver MECC. A recent review, collating all studies examining the effect of MECC training on the confidence and competence of trainees [22], did little to explain what elements worked for whom, in what circumstances, and why, which is particularly concerning given the aforementioned diversity in approaches to MECC training.

Thus, to address this explanatory gap about the mechanisms of HCS training within different contexts, the current study adopts a realist evaluation approach to understand ‘*what* [elements of HCS training] *works, for whom, under what circumstances, in what respects, to what extent, and why?*’ [32]. This evaluation will compare service providers from the VCSE, who are often highly experienced in interacting with service users but may not be confident in health promotion, with undergraduate pharmacy students, who have a healthcare background but may have little experience of interacting with service users. Pharmacy students have been selected as the healthcare professional comparison group as there is no available MECC literature that focuses on pharmacists despite implementation of MECC within this area [5,22]. This realist evaluation will test and refine programme theory explaining how and why HCS training enables MECC delivery. The resulting programme theory will inform on how HCS training as a workforce intervention can be adapted for different audiences, to make sure that it equips all recipients with the knowledge, confidence, and motivation to deliver MECC. It is therefore noteworthy that evaluating behavioural outcomes of recipients of MECC conversations is beyond the scope of this study. Nonetheless, the findings will facilitate the future evaluation of MECC delivery in the VCSE by exploring whether HCS training is sufficient for MECC delivery. Practically, this evaluation will also inform to what extent HCS training can be adapted (or shortened) without losing its impact. The findings will also provide utility for other approaches to MECC training, by identifying important elements needed to equip staff to deliver MECC. More broadly, understanding how HCS training shapes the delivery of MECC as situated as a brief, low intensity intervention is important for clarifying its intended function and mechanisms in practice.

## Methods

A realist evaluation approach has been selected as appropriate for the current study. Namely, the realist evaluation will test and refine initial programme theories (IPTs) using context, mechanism, outcome (CMO) configurations [33], which have been developed through stakeholder involvement and scoping of the existing literature. These CMOs describe in-depth, in written format, the specific context that is required for a specific part of the HCS training (mechanism resource) to create a specific response (mechanism reasoning) that results in the desired outcome. Importantly, individual CMO configurations will also be presented visually through an overall programme theory for each participant group. RAMESES II guidance [34] was adhered to for reporting of this protocol, and the checklist will be completed on publication of the final publication of the evaluation and its findings. Prior to data collection for interviews and before accessing the quantitative data, the evaluation was pre-registered on Open Science Framework (OSF): https://osf.io/wpbn3/overview. Recruitment and data collection began in August 2025 and is ongoing, due to be completed by July 2026. Results are expected by March 2027.

### Study design

This study is a concurrent mixed methods realist evaluation, consisting of two methods of data collection: 1) a quantitative before and after survey, and 2) qualitative interviews with trainees. Both methods of data collection will sample VCSE service providers and pharmacy students evenly, for comparison. The quantitative survey will be used to generate data on the extent and distribution of outcomes and how these differ between VCSE service providers and pharmacy students (context) [35], whilst the realist interviews will help to explain how and why these outcomes are produced, by linking them to CMO configurations. The quantitative survey was designed to be complimentary to existing evaluations of HCS training, to also aid comparison between groups of trainees [25,28,31]. A between-subjects design for the quantitative survey will aid comparison between participant groups. Ethical approval has been obtained from Northumbria University prior to recruitment and data collection (Project ID: 10429).

### Study setting

Data collection will utilise scheduled (for the quantitative surveys) and previously delivered (for the interviews) HCS ‘lite’ training across Portsmouth, delivered by Portsmouth City Council. Portsmouth covers a diverse area in the South of England, although is currently in the early stages of implementation to the VCSE. Additionally, training will be delivered to pharmacy students at Newcastle University, which is situated in the North East of England and is surrounded by rural and coastal communities. Both settings were selected for pragmatic reasons; utilising existing delivery of HCS ‘lite’ by [name] across Portsmouth, and opportunities to deliver HCS ‘lite’ in Newcastle, where the lead author (BN) is based.

### Participants

All participants must be over 18 and have attended (or about to attend) HCS ‘lite’ training in Portsmouth, delivered by [name]. Additionally, participants must either be a pharmacy student or work or volunteer within the VCSE at the time of receiving HCS ‘lite’ training.

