Why	• Based on social cognitive theory and experiential learning pedagogy. The goal is to provide trainees with the confidence to deliver healthy conversations, by immersing themselves in the skills and approach. • The philosophy is focused on four main pillars; 1) I am not responsible for the choices people make, 2) Being given information alone does not make people change, 3) People come to us with solutions, and 4) It is not possible to persuade people to change their habits. • The four target skills are; asking open discovery questions (ODQs), active listening, supporting SMARTER goal setting, and reflection on practice.
What	**Procedure:** • The training begins by centring itself around the unifying motivation to help people. The concept of MECC and its benefits are introduced briefly. The philosophy and skills are introduced using interactive activities. • Throughout the training, trainees are encouraged to think holistically about their own wellbeing and what they could do to support it. E.g. trainees practise having a healthy conversation in pairs before and after the training content, and are encouraged to audio-record the conversations to listen back and reflect on them as a pair. • Scenarios are presented and trainees are asked to respond by text on their phone and self-assess their response in accordance with the HCS approach. To facilitate psychological safety, HCS ‘lite’ deliberately does not include group feedback or modelling of an incorrect approach to a conversation. • Trainees map influences of health onto the Dalgren and Whitehead social determinants of health model [40] during a group activity. • Trainees are encouraged to consider one thing they will implement after the training. **Materials:** A SMARTER goal setting sheet is provided. After training, trainees are provided with a cue card containing the philosophy and key skills.
Who Provided	Mostly a Public Health Practitioner from Portsmouth City Council. Some sessions delivered to undergraduate pharmacy students adopt a ‘train the trainer’ approach whereby previous cohorts of undergraduate pharmacy students were trained by [name] to deliver HCS ‘lite’ training to their peers.
How	In person, group-based (to allow for peer learning and support), usually in groups of around 6–30 people. Chairs are formed in an arc so that all trainees face each other, to facilitate discussion, avoiding use of notes and laptops, and aiding a supportive and non-judgmental group setting.

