Where	Where all trainees are from the same organisation, training is delivered within a collaborative room within that organisation. For mixed groups (e.g., from some VCSE service providers), a room is booked that is accessible to all trainees (e.g., in a council building).
When and How Much	One three-hour session.
Tailoring	‘Train the trainer’ sessions are sometimes tailored so that undergraduate pharmacy students can take ownership of the training.
Modifications	Due to timetabling, undergraduate pharmacy students generally receive HCS ‘lite’ training in large groups, whilst VCSE service providers often attend HCS ‘lite’ training as part of a mixed group containing service providers from a range of professions, although the training is also often delivered to specific VCSE organisations.

Table 1 in Nichol et al. [21], which depicts regional MECC training according to the TIDieR checklist, illustrates the contrast with HCS training. Whilst both provide information about MECC and discuss health inequalities, regional MECC training focuses on providing information that can enable trainees to provide advice, whilst HCS (including HCS ‘lite’) training focuses on the skills needed to encourage individuals to identify their own needs for behaviour change.

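### The eligibility rule (Portsmouth, one named trainer) contradicts the planned Newcastle and peer-led pharmacy sessions, and the group comparison has no term for site or trainer

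*Protocol article*

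**What the plan says.** The Participants section sets one rule on site and trainer for everyone: "All participants must be over 18 and have attended (or about to attend) HCS ‘lite’ training in Portsmouth, delivered by [name"]. It then adds group membership: "participants must either be a pharmacy student or work or volunteer within the VCSE at the time of receiving" the training. The section on HCS 'lite' training describes delivery in the same way, as Portsmouth sessions given by one author.

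Three other places describe something wider.

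- Study setting: "Additionally, training will be delivered to pharmacy students at Newcastle University, which is situated in the North East of England". The section treats this as a second setting: "Both settings were selected for pragmatic reasons".
- Table 2, row on who provides the training: "Mostly a Public Health Practitioner from Portsmouth City Council". For some pharmacy sessions, "previous cohorts of undergraduate pharmacy students were trained by [name] to deliver HCS ‘lite’ training to their peers".
- Table 2, row on tailoring: "Train the trainer’ sessions are sometimes tailored so that undergraduate pharmacy students can take ownership of the training".

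The survey section invites every eligible trainee in the study period, so the eligibility wording decides who enters the analysis. The regression comparing the groups after training controls for baseline value, age and gender. The article states no term for site, trainer or session.

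**The concern.** The rule and the delivery plan cannot both hold as written. A pharmacy student trained at Newcastle fails the rule on site, whoever teaches there. A student taught by peers fails it on trainer, because Table 2 has the named person training the peer trainers, not delivering those sessions.

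Reconciling the text by including these students leaves a second difficulty. Newcastle and peer-led delivery, the latter sometimes tailored, are described only for pharmacy students, whereas VCSE training is described only in Portsmouth. A difference between the groups could then come from trainee background, from where and by whom the training was given, or from both. The Study design section presents the group contrast as a contrast of context, and the Discussion explains it by background and by experience with service users. The article itself lists modelling of the skills by the trainer as part of the training, so an effect of who delivers it is plausible.

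**Working it through.** **The texts side by side**

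| Feature | Participants section | Elsewhere in the article |
|---|---|---|
| Site | Portsmouth, all participants | Portsmouth, plus Newcastle University for pharmacy students (Study setting) |
| Trainer | One named person | Mostly the council practitioner; some pharmacy sessions by student peers (Table 2) |

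**Inputs from the article** (survey section): d = 0.3, power 80%, two-sided 0.05, two-group t test, 176 per group (352 in total).

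**The plan's own figure.** Solving the two-sample t test (noncentral t) for n gives 175.4, rounded up to 176 per group and 2 × 176 = 352 in total. Power at 176 per group is 0.801. The stated figure reproduces.

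The article does not give the share of pharmacy students trained at Newcastle or by peers, nor any effect of site or trainer. Everything below therefore rests on assumed ranges.

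**(a) Rule applied literally, excluded students not replaced.** VCSE stays at 176 and pharmacy falls to 176 × (1 − share excluded). Power is for d = 0.3.

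| Share excluded | Pharmacy n | Power |
|---|---|---|
| 0% | 176 | 0.80 |
| 10% | 158 | 0.78 |
| 25% | 132 | 0.74 |
| 50% | 88 | 0.63 |
| 75% | 44 | 0.43 |

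**(b) Rule not applied, students included.** If a share s of the pharmacy group has delivery that shifts scores by e SD, the group difference is biased by s × e. With 176 per group, the standard error of the difference is √(2/176) = 0.1066 SD. With no true difference, the probability of a significant result is 1 − Φ(1.96 − s·e/0.1066) + Φ(−1.96 − s·e/0.1066).

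| s | e (SD) | Bias (SD) | Type I error |
|---|---|---|---|
| 10% | 0.2 | 0.02 | 0.054 |
| 10% | 0.3 | 0.03 | 0.059 |
| 25% | 0.2 | 0.05 | 0.076 |
| 25% | 0.3 | 0.075 | 0.108 |
| 50% | 0.2 | 0.10 | 0.155 |
| 50% | 0.3 | 0.15 | 0.291 |

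For example, with s = 0.5 and e = 0.3, 0.15/0.1066 = 1.407, and 1 − Φ(0.553) + Φ(−3.367) = 0.29. These figures are for the unadjusted two-group comparison on which the sample size is based. Adjusting for baseline, age and gender does not remove a delivery effect that acts after baseline.

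**The case against.** The strongest reply is that literal exclusion is unlikely. The Study setting section, immediately before the rule, names Newcastle and says that both settings were chosen, and the survey section has a university contact sending out links. The natural explanation is that the eligibility sentence does not reflect the second site. This stands as a reading of intent, but it does not make the rule correct.

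A reader might infer from (a) that the study will be underpowered. The document does not support that. The target is a number to recruit, so excluded students could be replaced, and the article already says how a shortfall would be handled.

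The survey's role is also modest. The between-group tests are labelled exploratory, the Triangulation section says that the survey will not specifically test the programme theories, and the Discussion concedes that context is more than job role. Table 2 discloses the delivery differences. This lowers the stakes and stands, although the stated limitations mention neither site nor trainer, and the analysis text also says that testing will support or refute the theories.

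Two further inferences go too far. One is that large sessions occur only among pharmacy students. Table 2 says that they generally train in large groups, gives no separate size for VCSE sessions, and quotes around 6–30 overall. The other is that trainer and group are fully confounded. The article does not say who teaches at Newcastle, where the peer-led sessions take place, or whether they fall within the survey period. The named trainer may teach at both sites.

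Finally, the survey items are in registration files that are not shown, so site or session may already be recorded.

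**Conclusion.** The contradiction is firm: the eligibility rule as written would exclude participants whom the plan describes recruiting. The confounding is real in kind but of unknown size. It arises only if those students are included, and it is partial if some pharmacy students are trained in Portsmouth by the same trainer as the VCSE group. If all pharmacy students are trained at Newcastle, site and group coincide completely and no adjustment can separate them.

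Over the assumed ranges, the consequence runs from negligible (power 0.78, or bias 0.02 SD with type I error 0.054) to serious (power 0.43, or bias 0.15 SD, which is half the effect the study is powered for, with type I error about 0.29). The upper end should not be read as an estimate. Because the contrast is exploratory and non-randomised, this should be fixed but does not invalidate the study.

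**What to change.** 1. Reconcile the Participants section, and the matching description of the training, with the Study setting section and Table 2. State which sites and which deliverers make a trainee eligible, as the investigators intend. Whether peer-trained students are admitted is theirs to decide.
2. Record site, trainer type and session for each participant, if this is not already done.
3. If peer-trained students are eligible, pre-specify a sensitivity comparison of the two groups restricted to practitioner-led sessions, and report pharmacy results by site and trainer type.
4. Describe the main contrast as a comparison of the groups as delivered, not of trainee background alone. State as a limitation that site cannot be separated from group where the two coincide. The restricted comparison does not solve this if the practitioner-led pharmacy sessions are all at Newcastle.

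The cost is a change to the eligibility wording with an ethics notification, three session-level variables, one extra model and a limitation sentence. The restricted comparison will be less precise. The article gives July 2026 as the end of data collection, so the variables are easiest to capture while collection is under way.
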